### Technology acceptance survey

User acceptance of the TRANSFoRm tools will be measured in a centrally coordinated technology acceptance survey. The Technology Acceptance Model (TAM) questionnaire is a validated instrument for collecting *post hoc* perceptions of a technology artefact segregated into two domains: usefulness and ease of use [13-15]. Data will be collected retrospectively through an electronically distributed questionnaire to all intervention arm participants.

### User experience interviews

Clinician and patient experience with the TRANSFoRm tools will be assessed in follow-up, semi-structured, in-depth interviews with a purposive sample of interesting cases (i.e. GPs and patients with positive and negative experiences who demonstrated high/low usage patterns during the study). This interview study aims to assist interpretation of quantitative data generated by the main evaluation study by exploring: i) methods of recruitment and follow-up (e.g. web/mobile- vs. paper-based PROM); ii) reasons for any observed variations in recruitment performance across sites; iii) barriers and facilitators to successful recruitment; and iv) areas for improvements.

### Sample size

We estimated the average number of eligible GORD patients per primary care centre to be at least 100 during the 16-week recruitment phase, based on a conservative GORD prevalence of 10% [16] and a list size of 2,000 patients. We conducted a binominal power calculation taking into account the variation in centre characteristics. This showed that 536 participants across 40 centres, 20 per arm, will give the study 90% power to detect a 15% increase in recruitment, from 20% to 35%, using a conservative 5% intra-cluster correlation coefficient, at 5% significance level. Modelling conducted for the clinical study suggests that this will offer excess power to detect a clinically relevant change in self-rated health scores (±0.25 Reflux Disease Questionnaire points) between treatment groups.

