## Methods/design

### Trial design

We plan to conduct a 24-week, multi-centre, parallel-arm cluster randomised controlled trial of TRANSFoRm recruitment compared to GP-led opportunistic recruitment. The intervention arm will use the TRANSFoRm tools for participant recruitment, baseline data collection and follow-up. The control arm will rely on standard GP-led recruitment using web-based CRFs for baseline data collection and paper-based questionnaires for follow-up. The study will run in five countries (United Kingdom, The Netherlands, Belgium, Poland, and Greece) with eight primary care centres in each country, giving a total of 40 centres. Of these, 20 will be randomised to the TRANSFoRm arm and 20 to control on a 1:1 allocation ratio. Potentially eligible participants will be identified and recruited using TRANSFoRm or standard GP recruitment, with the hypothesis being that TRANSFoRm will yield 35% recruitment rate compared to 20% for the standard method. Participants will be finally randomised to on-demand or continuous use of PPI as part of the clinical protocol for the GORD study (Figure 3).

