### Statistical methods

The percentage of patients recruited to the study for the intervention and control groups will be calculated using descriptive statistics with 95% confidence intervals. These will be presented separately for each site, country and overall. The proportion of eligible participants recruited will be compared between groups using logistic regression, adjusted for clustering by centre by using generalised estimating equations (CI 95%, *P* < .05). Between-group differences in recruitment rate will be analysed using chi-square tests. This method will be also applied to compare the percentage of participants with complete data and the percentage of eligible patients who were recruited but later withdrew or lost to follow up.

Descriptive statistics will be used to outline the relative proportion of participants who were satisfied or dissatisfied with the TRANSFoRm tools as per item on the TAM questionnaire. Quantitative data will be analysed in STATA (v13) using an intention-to-treat approach.

Data from the user experience interviews will be audio-recorded, transcribed verbatim and analysed thematically using Ritchie and Spencer’s framework analysis approach [17].

The study has been designed and will be reported in CONSORT-compliant format [18].

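### The stated 536 participants give about 87% power, not 90%, on the plan's own inputs, and the paragraph does not say whether 536 counts eligible or recruited patients

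*Protocol article*

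**What the plan says.** The Sample size section of the protocol article starts from the expected flow of patients: "We estimated the average number of eligible GORD patients per primary care centre to be at least 100" over the 16-week recruitment phase. It then reports a binomial power calculation, said to allow for variation between centres, with the result that "536 participants across 40 centres, 20 per arm, will give the study 90% power to detect a 15% increase in recruitment". The rates compared are 20% and 35%, and the other settings are given as "using a conservative 5% intra-cluster correlation coefficient, at 5% significance level". The Trial design section confirms the allocation: "20 will be randomised to the TRANSFoRm arm and 20 to control on a 1:1 allocation ratio".

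The sentence after the power statement turns to the nested clinical trial: "Modelling conducted for the clinical study suggests that this will offer excess power" for a difference of 0.25 Reflux Disease Questionnaire points between treatment groups.

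The Primary outcome section defines the endpoint as the proportion of eligible patients who are recruited. The Statistical methods section compares that proportion by logistic regression with generalised estimating equations (GEE), 95% confidence intervals and a P threshold of .05, and also names chi-square tests. All of these are two-sided procedures. The Sample size section itself does not state sidedness.

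**The concern.** Every input needed to check the power claim is printed except sidedness, and the analysis section implies that. The printed result should therefore follow from the printed inputs, and it does not.

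The second problem is the unit. The denominator of a recruitment proportion is eligible patients. The PPI comparison can use only patients who were recruited and randomised. At the planned rates these two counts differ by a factor of about 3.6, so one number cannot serve both purposes. A reader cannot tell whether the clinical comparison was judged on about 147, 536 or about 1,100 patients.

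**Working it through.** **Inputs (protocol article).** Total 536; 40 centres, 20 per arm; 20% versus 35%; ICC 0.05; 5% level; target power 90% (Sample size, Trial design). Two-sided testing is inferred from Statistical methods. At least 100 eligible patients per centre are expected (Sample size).

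**1. Attempt to reproduce the 90%.**
- Mean cluster size m = 536/40 = 13.4; patients per arm = 268.
- Design effect = 1 + (13.4 − 1) × 0.05 = 1.62.
- Effective n per arm = 268/1.62 = 165.4.
- Sum of variances = 0.20 × 0.80 + 0.35 × 0.65 = 0.3875.
- Standard error = √(0.3875/165.4) = 0.0484; 0.15/0.0484 = 3.10.
- Power = Φ(3.10 − 1.96) = 87.3%.

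Other methods on the same inputs:

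| Method | Power with 536 |
|---|---|
| Normal, unpooled variance | 87.3% |
| Normal, pooled variance under the null | 86.7% |
| Arcsine | 86.9% |
| Logit | 85.6% |
| Continuity-corrected | 83.8% |
| Noncentral t, 38 df | 85.5% |
| Simulation, cluster-level t-test | 85.5% |
| Simulation, GEE robust Wald | 87.4% |
| Simulation, GEE with small-sample correction | 84.8% |
| One-sided 5%, unpooled / pooled | 92.7% / 92.4% |
| One-sided 5%, continuity-corrected | 90.4% |

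The simulation is beta-binomial with 20,000 replicates. No two-sided method reaches 90%.

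**2. Number needed for 90% with 20 centres per arm.**
- Under independence, n per arm = (1.96 + 1.2816)² × 0.3875/0.15² = 181.0 (unpooled), or 184.1 (pooled).
- Set 20m/(1 + 0.05(m − 1)) = n, so m = 0.95n/(20 − 0.05n).
- Unpooled: m = 15.7, total about 628.
- Pooled: m = 16.2, total about 650.
- Noncentral t, 38 df: m = 17.3, total about 692.

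**3. What would make 536 correct.** An ICC of about 0.037 (pooled) to 0.039 (unpooled) gives 90% at 536. The total also matches 2 × 185 × 1.45 = 536.5, where 1.45 is the design effect for 10 patients per centre. That would need 536.5/10, or about 54 centres, not 40. This origin is an inference; the document does not give it.

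**4. The unit of 536.**
- 536 eligible: recruited = 268 × 0.20 + 268 × 0.35 = 53.6 + 93.8, about 147.
- 536 recruited: eligible = 536/0.275, about 1,949, or 48.7 per centre. Design effect 3.39, effective n per arm 287.8, power about 98%.
- 100 eligible per centre: 4,000 eligible; recruited = 2,000 × 0.20 + 2,000 × 0.35 = 1,100. Design effect 5.95, effective n per arm 336.1, power about 99%.

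**The case against.** The strongest reply is that the error barely matters. Centres must be able to identify at least 100 eligible patients to take part, so the design expects about 4,000, more than seven times 536. Power is then about 99% at ICC 0.05. This stands, and it limits the point to a correction of stated figures. A reader might infer that the recruitment comparison is underpowered; the documents do not support that if the expected flow is met.

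Sidedness is the next reply. The hypothesis is directional and the Sample size section names no side. A one-sided 5% test gives about 92 to 93%, or 90.4% with continuity correction, so it would be wrong to say that no reading reaches 90%. But a one-sided calculation conflicts with the two-sided analysis described in Statistical methods.

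The word 'this' in the clinical-trial sentence may refer to the design as a whole and not to exactly 536 randomised patients. That is possible, although the number just before it is the natural referent. A reader might also infer that the excess-power claim is false. That cannot be shown: the article gives no standard deviation or required number for the questionnaire score and defers clinical details to a separate publication.

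A reader might think that the team could not tell when to stop recruiting. The documents do not support this, because recruitment ends after 16 weeks and not at a count of 536.

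Finally, matching centres within country could reduce between-centre variation. No gain is quantified, and the planned model is described as adjusting only for clustering by centre, so matching cannot be credited with the missing points. The stated allowance for centre variation does not help either: if it means unequal centre sizes, power would fall further, but no coefficient of variation is given.

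**Conclusion.** The concern holds as a correction of stated figures. With 536 eligible patients in 40 centres, 20% versus 35%, ICC 0.05 and a two-sided 5% test, power is about 87% by normal formulas and 85.5% with a t-test on 38 degrees of freedom. The shortfall is about 3 points, or 4 to 5 with the t-test. It rests on two-sided testing, equal centre sizes and no credit for matching.

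The unit of 536 also needs to be stated. This part rests on 'this' pointing back to the 536. What is established is that the paragraph does not keep eligible and recruited patients apart, not that the clinical comparison is too small.

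**What to change.** Rewrite the Sample size paragraph by unit:

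1. State that the calculation is two-sided and that its unit is the eligible patient. Then either keep 536 and report about 85 to 87% power, or report 628 to 692 eligible patients for 90% power with 40 centres, naming the method used.
2. Add that the expected 100 eligible patients per centre, about 4,000 in all, give about 99% power at ICC 0.05.
3. State separately how many patients are expected to be recruited and randomised (about 1,100 if 4,000 are eligible and the planned rates hold), and base the excess-power sentence on that number.

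The cost is recalculation and wording. No extra patients or centres are needed.

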### Randomisation, allocation and blinding

Primary care centres will be assigned to the TRANSFoRm or control arm on a 1:1 allocation ratio. The allocation sequence will be computer-generated using a within-country permuted random block design with blocks of two matched for list size, GORD prevalence, location, ratio of GORD appointments per week to list size and ratio of GPs to list size. The study is unblinded as it is impossible to blind primary care centres or investigators to the intervention. However, the allocation will not be shared with those involved in the data analysis to maintain objectivity and minimise bias.

### Statistical methods

The percentage of patients recruited to the study for the intervention and control groups will be calculated using descriptive statistics with 95% confidence intervals. These will be presented separately for each site, country and overall. The proportion of eligible participants recruited will be compared between groups using logistic regression, adjusted for clustering by centre by using generalised estimating equations (CI 95%, *P* < .05). Between-group differences in recruitment rate will be analysed using chi-square tests. This method will be also applied to compare the percentage of participants with complete data and the percentage of eligible patients who were recruited but later withdrew or lost to follow up.

Descriptive statistics will be used to outline the relative proportion of participants who were satisfied or dissatisfied with the TRANSFoRm tools as per item on the TAM questionnaire. Quantitative data will be analysed in STATA (v13) using an intention-to-treat approach.

Data from the user experience interviews will be audio-recorded, transcribed verbatim and analysed thematically using Ritchie and Spencer’s framework analysis approach [17].

The study has been designed and will be reported in CONSORT-compliant format [18].

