### Primary outcome

The primary outcome measure is the proportion of eligible patients successfully recruited using the TRANSFoRm method compared to standard GP-led opportunistic recruitment. A record of all identified, screened and successfully recruited patients will be kept using data from GP systems. The percentage of those recruited in the trial will be compared to identify whether TRANSFoRm yields a higher number of recruited patients compared to standard GP recruitment.

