### Secondary outcomes

Secondary outcomes will include the proportion of GORD cases recruited with complete baseline and follow-up data, as well as the proportion of those giving informed consent to participate but later withdrawing from the study. All electronic or paper-based CRFs completed by the recruited patients in each group will be reviewed, and retention data will be collected to examine whether there is a difference in the percentage of patients with complete data and the numbers of participants withdrawn or lost to follow up among the two arms.

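### An unadjusted chi-square test duplicates the centre-adjusted GEE model for recruitment and, on the natural reading, is the only test for completeness and withdrawal, although centres are randomised

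*Protocol article*

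**What the plan says.** All places are in the protocol article.

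- **Randomisation, allocation and blinding:** "Primary care centres will be assigned to the TRANSFoRm or control arm on a 1:1 allocation ratio". The sequence uses within-country blocks of two, matched on list size, GORD prevalence, location and two workload ratios.
- **Sample size:** the calculation is for "536 participants across 40 centres, 20 per arm", "using a conservative 5% intra-cluster correlation coefficient, at 5% significance level". The same section expects at least 100 eligible patients per centre over the recruitment period.
- **Primary outcome:** "The primary outcome measure is the proportion of eligible patients successfully recruited using the TRANSFoRm method".
- **Statistical methods, first test:** the proportion of eligible participants recruited is to be "compared between groups using logistic regression, adjusted for clustering by centre by using generalised estimating equations".
- **Statistical methods, next sentence:** "Between-group differences in recruitment rate will be analysed using chi-square tests". No adjustment for centre is mentioned.
- **Statistical methods, sentence after that:** "This method will be also applied to compare the percentage of participants with complete data", and likewise for patients who withdraw or are lost to follow-up.
- **Secondary outcomes:** completeness is "the proportion of GORD cases recruited with complete baseline and follow-up data". Withdrawal is counted among those who gave consent.

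**The concern.** A chi-square test treats every patient as an independent observation. Here whole centres are allocated, and the sample size section itself expects patients in one centre to resemble each other. The test therefore understates the standard error, and its p-values are too small whenever the ICC is positive.

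There are two consequences. For recruitment, the plan has two tests of one contrast and no rule for choosing between them. The Trial design section uses the term recruitment rate for the same 35% versus 20% comparison that defines the hypothesis, so the chi-square sentence cannot be set aside as being about something else. For completeness and for withdrawal or loss to follow-up, the chi-square appears to stand alone. Completeness is the study's second objective, so a chance difference between centres could be reported as an effect of the TRANSFoRm tools.

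**Working it through.** **Inputs.** 536 participants, 40 centres, 20 per arm, ICC 0.05, 5% level, at least 100 eligible per centre, recruitment 20% versus 35% (all from Sample size). The mean per centre is 536/40 = 13.4. Two-sided testing is assumed, because the section does not say.

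**The plan's own figure.** The usual two-sided pooled formula gives 185 per arm before clustering. With 20 centres per arm, the size needed per centre is 185 × 0.95 / (20 − 185 × 0.05) = 16.3, or about 654 in total, so 536 is not reproduced this way. A one-sided calculation with continuity correction comes nearest, at about 523, but neither choice is stated. The present point does not depend on this. It uses only the ICC and the centre sizes.

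**Formulas.** With m patients per centre, the design effect is DE = 1 + (m − 1) × ICC. The true error of an unadjusted test at nominal 5% is 2 × [1 − Φ(1.96/√DE)].

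**Recruitment, ICC 0.05, if the chi-square were relied on**

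| m | Source of m | DE | True error |
|---|---|---|---|
| 13.4 | 536/40 | 1 + 12.4 × 0.05 = 1.62 | 12.4% |
| 100 | eligible per centre | 1 + 99 × 0.05 = 5.95 | 42.2% |

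**Secondary proportions, ICC 0.05 borrowed from recruitment**

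The denominator is recruited patients, so m is smaller than the number eligible.

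| m | Source of m | DE | True error |
|---|---|---|---|
| 20 | 20% of 100 | 1.95 | 16.0% |
| 35 | 35% of 100 | 2.70 | 23.3% |
| 13.4 | 536 are the recruited | 1.62 | 12.4% |
| 2.68 | 20% of 13.4, if 536 are the eligible | 1.084 | 6.0% |
| 4.69 | 35% of 13.4, if 536 are the eligible | 1.1845 | 7.2% |

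**Check by simulation.** A beta-binomial simulation (20,000 runs, 20 centres per arm, equal or near-equal sizes, no matching) gave 12.4% to 12.7% at a mean of 13.4 per centre and 41.7% to 42.3% at 100. It gave 15.7% to 16.3% at 20 and 22.8% to 23.2% at 35.

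**Sensitivity to the ICC.** At ICC 0.01, DE is 1.124 for m = 13.4 and 1.99 for m = 100. The true error is then 6.5% and 16.5%.

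**The case against.** The strongest reply is that the primary outcome already has a valid analysis. The GEE sentence uses nearly the same terms as the primary outcome definition, and it is the only test sentence that carries a confidence level and a significance threshold. A reader might infer from the chi-square sentence that the primary test ignores clustering. The document does not support that. For recruitment, the chi-square is a second, conflicting test, and the inflation arises only if someone relies on it. This part of the reply stands. What remains is that no priority is stated.

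The phrase 'this method' can also be read as referring back to the GEE model. That is possible, but the chi-square sentence comes immediately before it and is the natural antecedent. On the kinder reading the text is still ambiguous about the test for every secondary proportion, and it needs the same correction.

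The sizes are also open to challenge, and this too stands in part. The protocol calls 0.05 conservative and gives no ICC for completeness or withdrawal. Matching within country may absorb some of the between-centre variation, which the formula and the simulation ignore. Both would lower the inflation.

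Finally, a fuller analysis plan may exist. It cannot remove the point, because the article does not leave the test open but names an unadjusted one.

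**Conclusion.** The point holds in this form. An unadjusted chi-square is prescribed in a centre-randomised trial. For recruitment it competes with a centre-adjusted GEE model, with neither named as decisive. For completeness and for withdrawal or loss to follow-up it is, on the natural reading, the only test.

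At ICC 0.05, without allowance for matching, relying on it for recruitment would raise the 5% error to between about 12% (13.4 per centre) and 42% (100 per centre). For the secondary proportions the range is about 6% to 23%, depending on how many patients are recruited per centre and on an ICC that is assumed for them. At ICC 0.01 even the 100-per-centre case falls to 16.5%.

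Two stronger readings should be avoided:

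- The 42% figure cannot be carried over to the secondary outcomes. It needs 100 patients per centre, which is the eligible denominator and not the recruited one.
- A reader might infer that the descriptive 95% confidence intervals by country and overall also ignore clustering. The article states no method for those intervals, so nothing can be concluded about their coverage.

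**What to change.** In Statistical methods:

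1. Delete the chi-square sentence.
2. Name the GEE logistic model clustered by centre as the only inferential test of recruitment.
3. Replace 'this method' with an explicit statement that the same clustered model, or an analysis of centre-level proportions, applies to baseline completeness, follow-up completeness, and withdrawal or loss to follow-up.

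The cost is a change of wording. The model is already planned and no new data are needed. Secondary p-values will tend to be larger than a chi-square would give, which is the intended result.

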**Methods/design:**

This multi-centre, parallel-arm cluster randomised controlled trial will compare TRANSFoRm-supported with standard opportunistic recruitment. Participants will be general practitioners and patients with gastro-oesophageal reflux disease from 40 primary care centres in five European countries. Randomisation will take place at the care centre level. The intervention arm will use the TRANSFoRm tools for recruitment, baseline data collection and follow-up. The control arm will use web-based case report forms and paper self-completed questionnaires. The primary outcome will be the proportion of eligible patients successfully recruited at the end of the 16-week recruitment period. Secondary outcomes will include the proportion of recruited patients with complete baseline and follow-up data and the proportion of participants withdrawn or lost to follow-up. The study will also include an economic evaluation and measures of technology acceptance and user experience.

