### Aim and objectives

The study described in this protocol aims to assess the effectiveness of TRANSFoRm in patient recruitment compared to standard GP-led opportunistic recruitment. The study hypothesis is that TRANSFoRm will increase patient recruitment by 15%, from 20% to 35%, compared to standard practice.

The objectives of the study are:To evaluate the effectiveness of TRANSFoRm in recruiting patients to clinical trials.To assess its effectiveness in collecting complete baseline and follow-up data.To compare the costs of recruitment in the TRANSFoRm and control arms.To explore practitioner and patient experience and acceptability of the system.

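### The withdrawal and loss-to-follow-up outcome is worded as a share of eligible patients in the statistical section but of enrolled patients elsewhere; read literally, higher recruitment looks like poorer retention

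*Protocol article*

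**What the plan says.** The protocol article describes the outcome in three places.

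- **Abstract, Methods/design:** "the proportion of participants withdrawn or lost to follow-up". The base is participants.
- **Secondary outcomes:** "the proportion of those giving informed consent to participate but later withdrawing from the study". The base is those who consented. The section then refers to "the numbers of participants withdrawn or lost to follow up among the two arms", again counting enrolled patients.
- **Statistical methods:** "the percentage of eligible patients who were recruited but later withdrew or lost to follow up". Read literally, the base is eligible patients.

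The Statistical methods sentence that contains this last phrase also covers a companion outcome, "the percentage of participants with complete data", whose base is participants. It applies a method carried over from the sentence before it, which names chi-square tests. The logistic regression with generalised estimating equations (GEE) for clustering by centre comes one sentence earlier still, for the primary outcome.

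Eligible patients are the proper base for the primary outcome, which is "the proportion of eligible patients successfully recruited using the TRANSFoRm method compared to standard GP-led opportunistic recruitment". Nothing in the article reconciles the three descriptions of withdrawal and loss.

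**The concern.** A retention measure should ask what happens to patients once they are enrolled. A patient who was never recruited cannot withdraw, so dividing withdrawals by all eligible patients mixes two quantities: how many were recruited, and how many of those left. The trial expects the first to differ sharply between arms, because that is its hypothesis. On the literal wording the primary effect would therefore enter a secondary outcome with its sign reversed. Equal retention would look like a disadvantage of TRANSFoRm, and a genuine retention benefit could be hidden. Follow-up is one of the two things the trial sets out to evaluate, so the outcome is not incidental.

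**Working it through.** **Inputs from the protocol article**

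- Recruitment: 20% control, 35% TRANSFoRm (Aim and objectives).
- Centres: 20 per arm (Trial design).
- Eligible patients: "the average number of eligible GORD patients per primary care centre to be at least 100 during the 16-week recruitment phase" (Sample size), hence 20 × 100 = 2,000 per arm.
- Intra-cluster correlation (ICC): 0.05, stated for recruitment (Sample size).
- Total of 536 participants (Sample size). If these are read as eligible patients, 536 / 2 = 268 per arm.

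**Assumed:** attrition among recruited patients. The article gives none, so 5% to 30% is used, equal in both arms. There is no stated figure for this outcome to reproduce.

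**Step 1. The two denominators**

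withdrawn / eligible = (recruited / eligible) × (withdrawn / recruited) = recruitment rate × attrition

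| Attrition, both arms | Control, of eligible | TRANSFoRm, of eligible | Ratio | Of recruited |
|---|---|---|---|---|
| 5% | 0.20 × 0.05 = 1.0% | 0.35 × 0.05 = 1.75% | 1.75 | 5% vs 5% |
| 10% | 2.0% | 3.5% | 1.75 | 10% vs 10% |
| 20% | 4.0% | 7.0% | 1.75 | 20% vs 20% |
| 30% | 6.0% | 10.5% | 1.75 | 30% vs 30% |

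The ratio is 0.35 / 0.20 = 1.75 whatever the common attrition.

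**Step 2. Break-even**

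The arms look equal when 0.35 × TRANSFoRm attrition = 0.20 × control attrition, so the attrition ratio must be 0.20 / 0.35 = 0.571. TRANSFoRm attrition must be 1 − 0.571 = 43% lower (5.7% against 10%, for example).

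**Step 3. A real benefit**

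Suppose attrition is 6% with TRANSFoRm and 10% in control. Of 2,000 eligible per arm, 700 and 400 are recruited, and 42 and 40 leave. The eligible base gives 42/2,000 = 2.1% against 40/2,000 = 2.0%. The recruited base gives 42/700 = 6% against 40/400 = 10%.

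**Step 4. Would the artefact be significant?**

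Take equal 10% attrition and 2,000 eligible per arm. The pooled proportion is 0.0275, and z = 0.015 / √(0.0275 × 0.9725 × 2 / 2,000) = 2.90. The design effect is 1 + (100 − 1) × ICC, and z is divided by its square root.

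| Setting | Design effect | z | p |
|---|---|---|---|
| 2,000 per arm, unadjusted chi-square | 1 | 2.90 | about 0.004 |
| 2,000 per arm, ICC 0.01 (assumed) | 1.99 | 2.06 | about 0.04 |
| 2,000 per arm, ICC 0.05 | 5.95 | 1.19 | about 0.23 |
| 268 per arm, unadjusted | 1 | 1.06 | about 0.29 |

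Unadjusted, z with 2,000 per arm runs from 2.04 at 5% attrition to 5.17 at 30%; with 268 per arm it runs from 0.75 to 1.89. Significance therefore varies with the setting, while the 1.75 ratio does not.

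**The case against.** The strongest reply is that the disputed phrase has a second reading. Eligible patients who were recruited may be the base, and later withdrawal or loss the event. Context supports this: the section that defines the outcome uses those who consented, the Abstract uses participants, and the companion outcome in the same sentence uses participants. Labels in the Statistical methods section are loose in any case, since it speaks of eligible participants where the Primary outcome section speaks of eligible patients. This stands. A reader might infer that the trial will certainly analyse withdrawal on all eligible patients. The article does not support that: it does not say that the statistical section overrides the outcome definition, and a statistical analysis plan that is not shown may settle it.

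What remains is that the literal reading is open. It has the same construction as the primary outcome, where eligible patients are the base and recruitment is the event.

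A reader might also infer that the artefact would produce a statistically significant harm, on the strength of p about 0.004. That figure ignores clustering. At the only ICC that the article states it becomes about 0.23. That ICC was given for recruitment, so applying it to attrition is itself an assumption, as is 0.01. The attrition rates are assumed too. The p-values are therefore illustrations only.

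Finally, recruited patients are a subset formed after centres were randomised, and the two recruitment methods may enrol different kinds of patient. The recruited base is therefore not a protected randomised comparison. This is true, but it is the quantity that the Abstract and the Secondary outcomes section describe.

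**Conclusion.** The concern holds as an unreconciled denominator. On its literal reading, the Statistical methods wording conflicts with the Secondary outcomes section and the Abstract, and the resulting measure equals recruitment times attrition. Under the trial's own 20% and 35%, equal attrition shows as a 1.75-fold excess against TRANSFoRm, and attrition must be 43% lower to look equal. Those two figures need only the hypothesised recruitment rates; the percentages and p-values also need the assumed attrition and, for significance, an ICC and a number of eligible patients.

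The clustering element also holds. The method carried over to this outcome is, on the nearest antecedent, an unadjusted chi-square test. Applied to patients nested in randomised centres, it gives intervals that are too narrow when outcomes are correlated within centres.

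The reach is limited to one secondary outcome. The primary outcome, the sample size and data collection are untouched. The sponsor should nevertheless correct it, because the wording can reverse or hide the conclusion on retention.

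**What to change.** In the Statistical methods section, define the outcome as the percentage of recruited (consented) patients who later withdrew or were lost to follow-up, in line with the Secondary outcomes section and the Abstract. State that it is analysed with the same logistic GEE model, clustered by centre, as the primary outcome, and not with an unadjusted chi-square test. If the share of all eligible patients who are recruited and retained is also of interest, report it as a separate outcome under its own label.

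The cost is one reworded sentence. No new data are needed, since the article already plans records of identified, screened and recruited patients and of retention. There are two small downsides. Confidence intervals will be wider than under the unadjusted test, and the report should say that the comparison describes those enrolled, a group formed after randomisation.
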